#### 2.1.3. Intervening Factors: Age, Religious Beliefs, Family Background, Level of Formal Education and Socio-Economic Status of the Adolescents.

**Study Area:** This study will be conducted in the Hoima District in Bunyoro region, because it is among the top five regions in Uganda with a high percentage of adolescent pregnancies, and hence, it is a representative region. Hoima has a higher percentage of adolescent pregnancies at 29% compared to the national level of 25% [4]. Access (5 km or more) to a public health facility by the population including adolescent girls is limited and it is estimated that approximately 39.5% of the population in the Hoima District live outside the catchment area (5 km or more) of public health facilities. This contributes significantly to inaccessibility and low utilization of SRH care among the adolescents who largely depend on financial support from the parents or guardians. This implies that the adolescent girls may not have the need for ASRH services met due to this hindrance [4].

The District has a thriving oil and tourism economic activities which increase the risk of vulnerability of the adolescent girls to risky sexual behavior. The Hoima District is located in Western Uganda, approximately 230 kilometers from Kampala. The District has a total geographical area of 5735.3 square kilometers and is bordered by Buliisa, Masindi, Kibaale, Kyankwanzi and Ntoroko Districts, and the Democratic Republic of Congo across Lake Albert. The District has a total of 36 registered secondary schools.

**Study Population:** 1080 adolescent girls aged 15–19 years attending secondary school in the Hoima District, Uganda.

### 2.2. Inclusion Criteria

Girls aged 15 to 19 completed years at the time of the studyCurrently in secondary school in the Hoima DistrictSchools enrolling both sexes or girls-only single sex schools will be includedAbility to read and write in the English languageFormal informed consent form signed by the parent or guardian for girls aged 15–17 yearsFormal informed assent form signed by girls aged 18 and 19 years

### 2.3. Exclusion Criteria

Girls below 15 years or above 19 completed years at the time of studyGirls who are unable to read and write English languageGirls with no formal informed consent from parent/guardian and herself

### 2.4. Sample Size

#### 2.4.1. Sample Size Calculation

The sample size will be calculated using the formula for comparing differences in rates and or proportions between two groups and determining the number of subjects per group *^n^*_Individual_Binary_ for a two-sided significance level *α* and power 1 − *β* [31]:$${}^{n}{}_{\mathrm{Individual}\_\mathrm{Binary}}=\frac{\left({}^{z}{}_{1-\alpha /2}+{}^{z}{}_{1-\beta }(2[{}^{\pi }{}_{T}(1-{}^{\pi }{}_{T})+{}^{\pi }{}_{C}(1-{}^{\pi }{}_{T})\right]}{{\left({}^{\pi }{}_{T}-{}^{\pi }{}_{C}\right)}^{2}}$$

#### 2.4.2. Considerations

*π*T = Proportion of pregnant girls in group 1 approximately 29% (0.29). This is the current pregnancy prevalence in Bunyoro region (29%).

*π*C = Proportion of pregnant girls in group 2 approximately 19% (0.19). This is the expected reduction in prevalence of adolescent pregnancy after the intervention.
$$\begin{array}{lll} \mathrm{Effect}\mathrm{size} & = & 10\%[\delta \mathrm{Binary}=(\pi T-\pi C)],\mathrm{which}\mathrm{is}0.1\\ \alpha & = & 0.05(\mathrm{two}-\mathrm{sided})\\ \beta & = & 0.2\\ Z\alpha /{}_{2} & = & \mathrm{Desired}\mathrm{significance}\mathrm{level}\mathrm{at}5\%(1.96)\\ Z_{1-\beta } & = & \mathrm{Desired}\mathrm{power}\mathrm{at}80\%(0.842)\\ \mathrm{Type}\mathrm{of}\mathrm{test} & = & \mathrm{Two}-\mathrm{sided} \end{array}$$

Absolute risk reduction = 10%;

**Step One:** Formula for determining the number of subjects per group *^n^*_Individual_Binary_ for a two-sided significance level *α* and power 1 − *β*:$$\begin{array}{c} =\frac{{\left(1.96+0.842\right)}^{2}[0.29(1-0.29)+0.19(1-0.19)]}{{\left(0.29-0.19\right)}^{2}}\\ =(2.802)2[0.2059+0.1539]\\ =(7.851\times 0.3598)/0.01\\ =282.5\\ \sim 283\mathrm{individuals} \end{array}$$

**Step Two:** In order to adjust for the clustering effect, the sample size (*^n^*_Individual_Binary_) was inflated by a Design Effect (DE) to get an adjusted sample size (*^n^*_Cluster_Binary)_ [31]. Therefore, to determine the adjusted sample size per study group (*^n^*Cluster_Binary) for a Cluster Randomized Controlled Trial (cRCT), with a binary outcome, we multiply it with the Design Effect (DE):*^n^*_Cluster_Binary_ = *^n^*_Individual_Binary_ × Design effect
*^n^*_Cluster_Binary_ = *^n^*_Individual_Binary_ × [1 + (*m* − 1) *ρ*]
where *m* is the fixed cluster size and *ρ* is the Intra-cluster correlation coefficient (ICC). ICC is the ratio of the between-cluster variance to the total variance of an outcome variance and quantifies the correlation between the outcomes of any two individuals within the same cluster [31]. Since there is no previously published data/study in Uganda documenting the ICC, an ICC of 0.01 was considered because it is within the recommended inter-quantile range ICC (0.011–0.094) for previously undocumented ICC. Campbell and Walters [24] recommended a minimum cluster size of 50 subjects per cluster to cater for secondary outcomes; therefore, a fixed cluster size of 60 individuals was considered for this study.
*^n^*_Cluster_Binary_ = *^n^*_Individual_Binary_ × [1+ (*m* − 1) *ρ*] = 282.5 × [1 + (60 − 1) × 0.01] = 449 adolescent girls per group = 449 × 2 = 898 individuals for the entire study (449 per group)

The final total sample size (898) will be increased by 10% to 988 participants to cater for a non-response insurance factor of 10%. Therefore, the treatment and control group will each have 494 adolescent girls.

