**Rationale:** This study is particularly important because it seeks to identify feasible and tested measures to promote safe sexual behavior intended to prevent adolescent pregnancy across the world. Uganda in particular has persistently had an unacceptably high adolescent pregnancy prevalence of 25% for the last 10 years compared to 16% globally [4]. This means that one in every four (25%) adolescent girls between 15 and 19 years in Uganda is pregnant or has had their first child. Despite the numerous studies that have been conducted worldwide and in Uganda on the use of school-based sexual and reproductive health services, school-based sexual and reproductive health programs are widely accepted as an approach to reducing high-risk sexual behavior among adolescents; however, these face numerous challenges in the implementation and scale-up because of the exposure of contraceptives to the school-going adolescents. In addition, incentive-based interventions that focus on keeping young people in secondary school generally reduce adolescent pregnancy; thus, there is a continued need to provide health services to adolescents using various approaches. Schools may be a good place in which to provide these services [29]. Therefore, this study focused in particular on the provision of comprehensive SRH package to adolescents in school for the reduction in risky behavior and prevention of pregnancy.

There is very limited evidence focusing on the provision of multiple interventions used in the prevention of adolescent pregnancy in both developing and developed countries. Therefore, this study therefore seeks to implement multiple interventions through a School-Based Sexual and Reproductive Health (SBSRH) model which will include both SRH information and services in selected secondary schools and will investigate the effects of providing SBSRH services on prevention of pregnancy among adolescent girls in school aged 15–19 years in the Hoima District, Uganda.

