## 2. Methodology

The study will use an experimental research design to assess the effect of the school-based SRH services on occurrence of the adolescent pregnancy among the school girls aged 15–19 years. The Cluster Randomized Controlled Trial (CRCT) design with qualitative and quantitative components will be used as a gold standard in conducting this impact evaluation research so as to maximize comparability between the intervention and control groups, and hence give a strong evidence of a causal relationship between the intervention and the outcome [30,31,32].

The unit of randomization will be the 18 clusters (school) and 1080 individuals (girls); therefore, the cluster (school) of the eligible girls will be randomly allocated to either the intervention (9 schools) or the control (9 schools) arms of the study.

Blinding will be done to prevent systematic biases stemming from foreknowledge of group allocations among the participants and research aim outcomes as per RCT study standards [31]. Pre-determined information, such as the research hypothesis, will be concealed from the participants, data collectors, teachers and data analysts so as to prevent biases at all levels of the research. The participants will not be made aware of the research hypothesis and will be assigned any group accordingly.

In order to avoid misleading biases, the study will use the Intent To Treat (ITT) approach for analysis. Every participant allocated to a treatment group is considered to be part of the trial. ITT will be used in an attempt to avoid potential bias and identify the true effect of the intervention.

The research will use a pre-test-post-test control group approach [33]. This is where pre-intervention (baseline) measures on the prevalence of pregnancy will be conducted to allow for explicit evaluation of the pre-to-post changes.

Qualitative data will be collected through in-depth interviews of key informants in the community and discussions with groups of adolescent boys, parents, community members and school leadership. Standard guides with open-ended questions will be used for conducting the interviews and discussions. The participants of the interviews and discussions will be purposively selected based on their role in preventing adolescent pregnancy in the community.

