#### 2.1.2. Dependent Variable: Prevention of adolescent pregnancy

Primary outcomes
(a)Incidence of pregnancy(b)Sexual and Behavior change(c)Utilization of SRH services

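### The sample size is built on a regional prevalence of girls who are pregnant or have had a child, but the primary outcome is new pregnancy over 12 months in schoolgirls, so the 80% power is unsupported for that outcome

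*Protocol article*

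**What the plan says.** Section 2.4.2 takes 29% as the proportion without intervention ("This is the current pregnancy prevalence in Bunyoro region (29"%) and 19% as the proportion with it ("This is the expected reduction in prevalence of adolescent pregnancy after the intervention"). The difference is given as "Absolute risk reduction = 10"%.

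The Rationale in the Introduction explains what the survey measures, for the national figure: "one in every four (25%) adolescent girls between 15 and 19 years in Uganda is pregnant or has had their first child". The Study Area text under Section 2.1.3 puts the local figure beside it from the same source: "Hoima has a higher percentage of adolescent pregnancies at 29% compared to the national level of 25% [4"].

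The primary outcomes in Section 2.1.2 are listed as "a)Incidence of pregnancy(b)Sexual and Behavior change(c)Utilization of SRH services", and Section 4 again expects a fall in incidence. Sections 2.7, 2.8 and 2.8.3 give 12 months of follow-up, and Section 2.2 restricts entry to girls currently in secondary school. Section 2 nevertheless describes the design in terms of prevalence: "pre-intervention (baseline) measures on the prevalence of pregnancy will be conducted to allow for explicit evaluation of the pre-to-post changes".

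**The concern.** Two different quantities share the word pregnancy. The 29% is a stock: it accumulates up to the survey date and describes girls of the region, whether or not they are in school. The primary outcome is a flow: new pregnancies during one year in girls who are enrolled. The article never turns the stock into a yearly risk and never gives a rate for girls in school.

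The control proportion and the difference determine the whole sample size. If the yearly risk in schoolgirls is well below 29%, the fixed 18 x 60 design has much less power for the same relative effect than the article states, and a non-significant result could be misread as evidence that the intervention does not work. The prevalence wording in Section 2 adds to this, because it leaves open whether pregnancies that began before the intervention count towards the comparison.

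**Working it through.** **1. The plan's own figure.** Inputs from Section 2.4.2: p1 = 0.29, p2 = 0.19, z-values 1.96 and 0.842, ICC 0.01, cluster size 60.

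- n per group = (1.96 + 0.842)² × (0.29 × 0.71 + 0.19 × 0.81) / 0.10² = 7.851 × 0.3598 / 0.01 = 282.5, stated as 283.
- Design effect = 1 + 59 × 0.01 = 1.59, and 282.5 × 1.59 = 449 per group, 898 in total.
- 898 × 1.10 = 988; 988/60 = 16.5, raised to 17 and then 18 schools, so 18 × 60 = 1080.

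The arithmetic reproduces. The difficulty is the input.

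**2. Power of the fixed design over a range of control incidence.** The control incidence c is an assumption, because the article gives none. The treated incidence is p = c × 19/29, which keeps the plan's relative reduction of 34.5%. With 10% non-response, 54 girls per school remain:

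- 9 × 54 = 486 per arm, design effect 1 + 53 × 0.01 = 1.53, effective n = 486/1.53 = 317.6.
- SE = √{[c(1 − c) + p(1 − p)] / 317.6}, ratio = (c − p)/SE.
- Normal power = Φ(ratio − 1.96). The t version uses a noncentral t with 18 − 2 = 16 degrees of freedom, and needs a ratio of about 2.98 for 80%.

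| c | p | ratio | power, normal | power, t | reduction needed for 80% (t) |
|---|---|---|---|---|---|
| 5% | 3.3% | 1.09 | 19% | 18% | 80% |
| 10% | 6.6% | 1.58 | 35% | 32% | 60% |
| 15% | 9.8% | 1.98 | 51% | 46% | 50% |
| 20% | 13.1% | 2.35 | 65% | 60% | 43% |
| 25% | 16.4% | 2.70 | 77% | 72% | 38% |
| 29% (plan) | 19.0% | 2.97 | 84% | 80% | 35% |

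Example at 10%: SE = √[(0.0900 + 0.0612)/317.6] = 0.0218; 0.0345/0.0218 = 1.58.

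**3. The absolute effect.** A 10-point fall cannot occur if c is below 10%. At exactly 10% it needs every pregnancy prevented, at 15% a 67% reduction (10/15) and at 20% a 50% reduction (10/20).

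**4. If the endpoint were ever-pregnant prevalence in the same girls.** It could not fall below its baseline. Take 29% at baseline in both arms and an assumed 10% incidence in the remaining 71%. The arms end at 0.29 + 0.71 × 0.10 = 36.1% and 0.29 + 0.71 × 0.0655 = 33.7%. That is 2.4 points apart (0.71 × 0.0345), with about 10% power even at 60 girls per school. Preventing every new pregnancy would separate them by 0.71 × 0.10 = 7.1 points.

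**5. What yearly risk a 29% stock might imply (illustration only).** Assume ages spread evenly over five years and a constant hazard h, and solve mean exp(−ht) = 0.71. With exposure from age 15, h = 0.146 and the 12-month risk is 13.6%. With exposure from age 13, h = 0.0775 and the risk is 7.5%. If the hazard instead rises linearly with age, the mean 12-month risk among girls not yet pregnant is 21.1% and 14.2%.

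**The case against.** Section 2.4 compares two groups, so 29% against 19% can be read as control against intervention at 12 months rather than as a fall over time. A reader might infer that such a difference cannot be observed. The article does not support that: it is strictly true only for ever-pregnant prevalence in a followed cohort, and the stated outcome is incidence. For incidence, a 10-point fall is ruled out only below 10% control risk.

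A reader might also infer that 29% is far too high for one year. The article gives no incidence, so 29% is unsupported rather than disproved. Step 5 depends on the hazard shape. The survey measure omits earlier pregnancies that did not lead to a birth, and Section 2.6 picks schools with the highest dropout rates; both could push the rate up, while restriction to girls still in school could push it down.

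The plan states its effect as an absolute difference. With 10 points kept, power is high wherever the difference is possible (about 94% at 20% control incidence with 54 girls per school), but only by assuming the larger relative reductions in step 3, which the article does not justify.

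It is tempting to predict an uninterpretable null, or to put a size on dilution from pregnancies present at baseline. Neither follows. A null with a confidence interval can be interpreted, and the article gives no baseline pregnancy rate. Incidence, properly counted, excludes those pregnancies.

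The definition of the survey measure is written out only for the 25%. Its extension to the 29% rests on the side-by-side comparison and shared citation, which is a sound but inferred link.

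What stands against the plan is the mismatch. An analysis plan could tighten the endpoint, but the sample-size input is fixed and labelled as prevalence here.

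**Conclusion.** The concern holds as a mismatch between the sample-size input and the primary outcome. The 80% power describes a contrast in a regional stock measure, not 12-month incidence in schoolgirls, and no step in the article links them. Confidence is high on the mismatch and lower on its size. Under the plan's relative reduction, ICC 0.01, nine schools per arm and 54 girls per school, normal-approximation power runs from about 19% at 5% control incidence to 77% at 25%, and t-based power from 18% to 72%. It is therefore below 80% across that range, but the true control incidence is not known from the documents. This should be corrected before the stated power is relied on.

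**What to change.** - State the primary pregnancy outcome as a new pregnancy beginning after baseline and by 12 months, compared between arms, and bring the pre-to-post prevalence wording in Section 2 into line with it.
- State that girls already pregnant at baseline do not count as events, and reconcile their handling with the intention-to-treat statement in Section 2. Section 2.7 describes school allocation before recruitment and the baseline survey, and the questionnaire is self-administered, so removing girls on reported pregnancy could select differently by arm. The rule should say how this is addressed.
- Replace 29%/19% with an assumed 12-month incidence in schoolgirls, with its justification, shown over a range.
- Restate the power, or the detectable relative reduction, of the fixed 18 x 60 design over that range.

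The cost is protocol wording and a recalculated power table. Baseline pregnancy is already to be measured, so no new data collection is needed. The downside is a lower stated power and, if girls pregnant at baseline leave the at-risk group, a slightly smaller denominator.

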However, adolescent pregnancies may occur as a result of other factors: customs and traditions that lead to early marriage, adolescent sexual behavior, which may also be influenced by alcohol and drugs, lack of education and information about reproductive sexual health, lack of access to tools that prevent pregnancies, peer pressure to engage in sexual activity, incorrect use of contraception, sexual abuse that leads to rape, poverty, exposure to abuse, violence, family strife at home, low self-esteem and low educational ambitions or goals [9,10]. It is also important to note that adolescent pregnancy is not always a result of a deliberate choice; often, unintended pregnancy among adolescent girls is a consequence of little or no access to Adolescent Sexual and Reproductive Health (ASRH) information and services [3]. The majority of adolescent girls who become pregnant are married and/or pressured to have a child, while for others, pregnancy often results from abusive, forced or coerced sex [11]. The limited awareness on consequences of adolescent pregnancy, inaccessibility to ASRH services and social protection of the adolescent girls within the community increases the risk of becoming pregnant [3].

In sub-Saharan Africa, adolescent births are more likely to occur among poor, less educated and rural populations because of reasons including lack of access to contraception, early marriage, poor or limited access to education, cultural norms and poverty, to mention but a few [12,13]. An adolescent pregnancy poses a challenge to maternal and child survival, because pregnant adolescents and adolescent mothers are likely to be uneducated, unemployed and poor and might not seek or utilize health care services for either themselves or their newborns’ at critical times [14,15]. Thus, increased risks of maternal morbidity and mortality have been noted among pregnant and adolescents mothers [16]. This means that efforts to reduce maternal and child mortality need to focus on adolescents girls too.

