Adolescent pregnancy and motherhood has detrimental socioeconomic and psychological outcomes for the young mother, her child, and her young siblings. When a girl becomes pregnant, her education may end, her job prospects diminish, she becomes more vulnerable to poverty, her health often suffers and the complications from pregnancy and childbirth are the leading cause of death among adolescent girls. The child on the other hand is likely to live in poverty, grow up without a father, become a victim of neglect or abuse, do less well at school, become involved in crime, abuse drugs and alcohol, eventually become a teenage parent themself and begin the cycle all over again [2,3].

The consequences of adolescent pregnancy include premature births, low birth weight of the newborn, high risks for medical complications such as obstructed labor, obstetric fistula, leakage of urine and/or feces and mortality [9]. Adolescent girls account for 14% of the estimated 20 million unsafe abortions performed each year, which result in approximately 68,000 deaths. This is an alarming public health problem globally and requires urgent multi-sectoral attention [9].

In 2013, there were nearly 300,000 abortions in Uganda, which is equivalent to 54 abortions per 1000 women of reproductive age, or one abortion for every 19 such women. This rate is far higher than the average rate for Eastern Africa, which is 36 abortions per 1000 women [17]. In addition, the Ministry of Health in Uganda estimated that abortions accounted for 26% of maternal mortality in 2008; this is higher than the 18% in the Eastern African region and the 13% in the world as a whole [1,17]. The Uganda Demographic Health Survey (UDHS), conducted in 2016, estimated the pregnancy-related mortality ratio to be at 368 death per 100,000 live births and adolescents 15–19 years contributing 17% of all pregnancy related mortality rate in Uganda. Additionally, 15 out of every 1000 Ugandan women of reproductive age were treated for abortion complications that year [4]. Therefore, it is paramount to pay special attention to adolescents to prevent maternal mortality due to unsafe abortions among the adolescents.

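### The sample size takes a cumulative, all-girls pregnancy prevalence (29%) as the 12-month rate in enrolled schoolgirls, so the stated 80% power is unsupported

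*Protocol article*

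**What the plan says.** Section 2.4.2 of the protocol article sets the two rates as "Proportion of pregnant girls in group 1 approximately 29% (0.29") and "Proportion of pregnant girls in group 2 approximately 19% (0.19"). It describes the second as the level expected after the intervention, so the first is the no-intervention rate, although it carries the symbol πT. The effect is fixed on the absolute scale: "Absolute risk reduction = 10" per cent. The source of the first rate is given as "This is the current pregnancy prevalence in Bunyoro region (29" per cent).

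Two other places show what that figure measures. The Study Area paragraph under Section 2.1.3 sets it beside the national figure, from the same cited survey: "Hoima has a higher percentage of adolescent pregnancies at 29% compared to the national level of 25" per cent. The Rationale in the Introduction explains the national figure as one in four "adolescent girls between 15 and 19 years in Uganda is pregnant or has had their first child".

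The trial measures something else. Section 2.1.2 lists incidence of pregnancy first among the primary outcomes. Section 2.2 restricts entry to girls currently in secondary school, and Section 2.8 gives 12 months of follow-up.

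**The concern.** The planning rate and the outcome differ in two ways. The first is time: a count of girls who are pregnant or already mothers accumulates every year since each girl was first at risk, whereas the trial counts pregnancies over one year. The second is population: the survey figure covers girls in and out of school, whereas the trial enrols only girls in school.

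The Introduction gives reasons to expect a lower rate in school. It says "The majority of adolescent girls who become pregnant are married and/or pressured to have a child", and also "When a girl becomes pregnant, her education may end". Table 1 lists, as interviewees, girls who left school for pregnancy-related reasons.

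At stake is the only statement of what the trial can detect on its headline outcome. If the 12-month rate in these schools is well under 29%, a non-significant result could easily come from a trial with modest power, yet readers relying on the stated 80% would give it more weight than it deserves.

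**Working it through.** **Inputs from the article.** Rates 0.29 and 0.19; two-sided α 0.05 (z = 1.96); power 80% (z = 0.842); ICC 0.01; cluster size 60; 10% non-response; 9 schools per arm (Sections 2.4.2 and 2.5).

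**The plan's figure, reproduced.**
- Per group before clustering: (1.96 + 0.842)² × [0.29 × 0.71 + 0.19 × 0.81] / 0.10² = 7.851 × 0.3598 / 0.01 = 282.5.
- Design effect: 1 + 59 × 0.01 = 1.59, and 282.5 × 1.59 = 449 per group.
- 898 × 1.10 = 988 in total; 988 / 60 = 16.5 schools, raised to 18, giving 1080 girls.

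The calculation is correct for its inputs. The problem lies in the 29%.

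**Power at other control rates, relative reduction carried over.** Assumptions: risk ratio 0.19/0.29 = 0.655 (a 34% fall), and 54 girls analysed per school (60 less 10%).
- Effective number per arm: 9 × 54 / (1 + 53 × 0.01) = 486 / 1.53 = 317.6.
- Power = Φ(|pC − pI| / SE − 1.96), with SE = √{[pC(1 − pC) + pI(1 − pI)] / 317.6}.
- Example at 15%: pI = 0.0983, difference 0.0517, SE = √(0.2161 / 317.6) = 0.0261, ratio 1.983, power Φ(0.023) = 51%.

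| Control rate | Intervention rate | Power |
|---|---|---|
| 5% | 3.3% | 19% |
| 10% | 6.6% | 35% |
| 15% | 9.8% | 51% |
| 20% | 13.1% | 65% |
| 29% | 19.0% | 84% |

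Power reaches 80% at a control rate of about 26.5%, or about 25% if all 60 girls per school are analysed.

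**Power with the stated 10-point absolute reduction kept (same 54 per school).**
- 20% v 10%: power 95%, a 50% relative fall.
- 15% v 5%: power 99%, a 67% relative fall.
- 10% v 0%: every pregnancy prevented.

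**Smallest reduction detectable with 80% power (same settings).** 10% to 4.3% (57% relative), 15% to 8.0% (47%), 20% to 11.9% (40%).

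**Illustrative conversion of 29% to a yearly rate.** The article gives none, so this is assumption only. Let the hazard h be constant from a starting age a₀, with ages spread evenly over 15 to 20 years, and solve for the h at which the mean of 1 − exp(−h(age − a₀)) equals 0.29. The yearly risk 1 − exp(−h) is 6.1%, 7.5%, 9.6% and 13.6% for a₀ = 12, 13, 14 and 15. A hazard that rises linearly from age 13 or 15 gives about 14% or 21% in girls never pregnant. All of these refer to girls in general, not schoolgirls, and all lie below 26.5%.

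**The case against.** **The effect is absolute in the plan.** Section 2.4.2 fixes 10 points and mentions no relative reduction. On that scale power rises as the control rate falls. This stands: the low power figures hold only if the relative effect carries over. What remains is plausibility, since 10 points at 15% or 20% asks for a 67% or 50% relative fall where the plan's own rates imply 34%.

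**No 12-month rate is given.** A reader might infer that the trial is certainly underpowered, or that the rate among enrolled girls must be far below 29%. The article does not establish either. The illustrative conversions run from about 6% to 21%. Section 2.6 also selects schools with the highest dropout, in a district whose economy is said to raise girls' vulnerability. That could raise the rate above that of an average schoolgirl, by an amount the plan does not state.

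**The target is not impossible by construction.** A reader might infer that 29% to 19% cannot happen because an ever-pregnant proportion in a fixed cohort cannot fall. The formula compares two groups and does not require any cohort's proportion to fall, even though the pre-test/post-test language invites that reading. The narrower point stands: pregnancies before baseline cannot be prevented and would dilute the contrast between arms, so an ever-pregnant endpoint does not rescue the input.

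**The definition reaches the 29% by inference.** It is written for the national 25%, and the link is the shared source and the direct comparison in the Study Area paragraph. That is a fair reading, and no passage offers another.

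**Conclusion.** The point holds in conditional form. The 29% is a cumulative prevalence among all girls of the age group, used without conversion as the event rate for 12-month incidence in enrolled schoolgirls, so the 80% power is unsupported. It has not been shown to be wrong by any fixed amount. For control rates of 10% to 20%, power is about 35% to 65% if the 34% relative reduction carries over; it is preserved only if the intervention achieves a much larger relative fall. These figures assume ICC 0.01, 54 girls analysed per school, equal cluster sizes and a normal approximation. The fault is in an input that the article states, so it is not a detail left to a fuller document.

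**What to change.** In Section 2.4.2:
- Replace 29%/19% with an assumed 12-month pregnancy proportion in enrolled schoolgirls and the reduction to be detected, labelled as absolute or relative, with the reasoning for both.
- Keep 18 schools and 1080 girls. Restate power and the smallest detectable reduction over a range of control rates, for example 10%, 15% and 20%, with 5% as a pessimistic bound.
- Withdraw the 80% power claim unless the stated rate supports it.
- If the baseline survey is used to inform the rate, pool it over both arms and treat it only as a lower bound: girls who became pregnant and left school are absent from it. Pooled 6-month data, examined without regard to arm, give a further check.

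The cost is rewording one section and adding a short table. No schools, girls or visits are added. The downside is that the stated power becomes less favourable.
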